# Effectiveness of a pressure-sensing mattress system for reducing the risk of pressure ulcer formation by lowering interface pressure in vulnerable patient populations: Parallel-two-group randomized trial

## Abstract

**Background:** Pressure ulcers are a significant challenge in healthcare, resulting in substantial financial costs to hospitals and personal costs borne by affected patients and their families. Continuous pressure imaging (or interface pressure mapping) of the interface pressure between the body and support surface could be an effective technology as part of an overall strategy for the prevention and management of ulcers. This randomized controlled trial builds on previous research to establish the effectiveness of XSENSOR Technology Corporation's ForeSite PT™ system, a continue pressure imaging technology, in its ability to reduce interface pressure and reduce the incidence of pressure ulceration.

**Methods:** A parallel two group randomized controlled clinical trial will be conducted. A total of 600 eligible consenting inpatients at a tertiary care institution will be randomly allocated to either have the ForeSite PT™ system and the LCD monitor turned on (intervention group), or have the ForeSite PT™ system and the LCD monitor turned off (control group) in a ratio of 1:1. Both groups will be included in the study up to a maximum of 7 days. In addition to interface pressure, clinical outcomes will also be measured at baseline (within 24 hours of admission) and on the last day of enrollment in the trial (within 24 hours prior to discharge, or on the seventh day (whichever comes first)). The perceptions of patients allocated to the intervention group, and the perceptions of healthcare providers each time a patient in their care is allocated to the intervention group, will be measured on the last day of enrollment in the trial or on the seventh day (whichever comes first).

**Discussion:** This will be the first randomized controlled trial to investigate the effectiveness of continuous pressure imaging on pressure management among, and the association between interface pressure and development of pressure-related skin and soft tissue change with potential for progression to overt pressure ulceration. The results could provide evidence to inform clinical practice guidelines on the prevention and management of pressure ulcers.

**Trial registration:** TBD

**Keywords:** Pressure ulcers, Bedsores, Continuous pressure mapping, Interface pressure imaging

## Background

Pressure ulcers are a leading cause of morbidity (and in some instances, mortality) in hospitalized and institutionalized patients (Woodbury), resulting in substantial financial costs to hospitals and personal costs borne by affected patients and their families. A pressure ulcer is "a localized injury to the skin and/or underlying tissue over a bony prominence, as a result of pressure, or pressure in combination with shear (NPUAP)." The size and severity of pressure ulcers vary, ranging from skin erythema to full thickness tissue loss with damage extending into muscle and bone (NPUAP Staging). Annually, there are

Ethics ID number: REB13-0794

Study Title: Effectiveness of a pressure-sensing mattress system for reducing the risk of pressure ulcer formation by lowering interface pressure in vulnerable patient populations: Parallel-two-group randomized trial

PI: [name]

Version number/date: V2 01/04/2014

an estimated 250,000 to 500,000 individuals affected by pressure ulceration in Canada, with the overall estimated prevalence in all health-care institutions to be 26.0% in Canada (Dealey, Wound Care in Canada).

Pressure ulcer development and recurrence is multi-factorial; however, they primarily occur in people who have limited mobility, nerve damage, or both. Risk factors include limited mobility and activity; perfusion (including diabetes); skin conditions; skin moisture and incontinence; advanced age; reduced levels of albumin, haemoglobin/anaemia, lymphocytes, and other blood serum components; compromised nutritional status; and general health status (Coleman, Dorner). Other predictors of pressure ulceration include ICU admission length, norepinephrine administration, and cardiovascular disease among adult critical care patients (Cox), while delayed and inappropriate medical management, history of or existing pressure ulceration, and limited independence in self-care were also predictors among adults with spinal cord injuries (Marin).

The economic impact of pressure ulcers is significant, as the estimated cost of treatment in the UK varies from £1,214 to £14,108 per case. The cost of treatment increases with severity as more severe cases require longer healing times and have higher incidence of complications (Dealey). The financial burden of pressure ulcers are also significant in the United States, where the average hospital treatment cost associated with stage IV pressure ulcers and related complications was \$129,248 for one hospital admission, and \$124,327 for those acquired in the community over four hospital admissions (Brem). In Canada, the estimated average monthly cost of pressure ulcer management among individuals with spinal cord injury was \$4,475, with hospital admission costs making up the greatest proportion of the total cost (Chan). The cost of nursing time, which is comprised of dressing the wound, repositioning the patient and monitoring and risk assessment, amount to the vast majority of resource cost of treatment (Dealey).

Many pressure ulcers are avoidable; however, it is generally accepted that there are situations where they cannot be prevented (Black, Langemo, NPUAP). There are various modalities to prevent and treat pressure ulcers, including wound cleansers, repositioning, negative pressure therapy, debridement, enteral and parenteral feeding, vitamin and mineral supplementation, specialized mattresses, support services, ultrasound therapy, honey, cellular therapy, musculocutaneous and fasciocutaneous flap closure; however, there is no widely accepted formal process for treatment (Levine). Rather, many acute care settings and long-term-care facilities adopt multi-pronged, multidisciplinary interventions to prevent pressure ulcers (Niederhauser). Current guidelines advise health care practitioners to conduct a standardized pressure ulcer risk assessment (Toolkit, SCI Guideline). The use of risk assessment scales provides a more accurate prediction of pressure ulcer risks than clinical judgment (Pancorbo-Hidalgo). The Braden Scale for Predicting Pressure Sore Risk (Bergstrom) is recommended as it has received the most validation and has demonstrated the best sensitivity/specificity balance and the highest predictive capacity (Pancorbo-Hidalgo). As applied pressure over a prolonged period is a primary cause of pressure ulcers, frequent and regular repositioning of the patient has been recommended as an integral

Ethics ID number: REB13-0794

Study Title: Effectiveness of a pressure-sensing mattress system for reducing the risk of pressure ulcer formation by lowering interface pressure in vulnerable patient populations: Parallel-two-group randomized trial

PI: [name]

Version number/date: V2 01/04/2014

component of prevention and treatment protocols. The best practices pertaining to a specific turning regiment varies from the National Pressure Ulcer Advisory Panel (NPUAP) recommending repositioning every two hours and the European Pressure Ulcer Advisory Panel (EPUAP) recommending every four hours. Thus pressure ulcer prevention and management are necessarily labour-intensive.

Continuous pressure imaging (or interface pressure mapping) of the interface pressure between the body and support surface could be an effective technology as part of an overall strategy for the prevention and management of ulcers. By placing a thin mattress or sensor pad with monitoring capabilities under a patient, pressure imaging interprets the interface pressures and provides the patient's real-time pressure points on a corresponding computer screen, which can assist healthcare providers determine when a patient should be re-positioned (Hanson). XSENSOR Technology Corporation designed the ForeSite PT™ Patient Turn System (here in "ForeSite PT™ system"), which can continuously monitor bed surface interface pressure and track the patient's exposure to that pressure. The ForeSite PT™ system provides patient turn tracking to assist with management of the patient turn schedule. The pressure exposure monitor provides a visual image that quantifies historical pressure information. The exposure monitor assists clinical staff by alerting them to the location of body areas that have experienced the greatest exposure to pressure. The surface pressure monitor provides clinical staff with a visual image of the pressure distribution across a patient's body. It can be used by care providers to identify high pressure areas in real time and to validate that patient repositioning has successfully relieved pressure.

The ForeSite PT™ system emerged, in part, from a partnership between the Ward of the 21st Century (W21C) and XSENSOR to support the development and commercialization of this technology. This project included focus groups; 1-1 meetings with clinicians, W21C leads and managers; usability testing sessions; heuristic evaluations for iterative technology development; a pilot and a natural history study; and concluded with the evaluation of the ForeSite PT™ system through focus groups, usability testing, and a pilot study. The proposed study will build on this previous research conducted with XSENSOR to establish the effectiveness of a pressure-sensing mattress system (ForeSite PT™ system).

The ForeSite PT™ system consists of two parts: a thin, flexible sensor overlay that is positioned under the hospital linen (under the fitted sheet) and an LCD monitor that is mounted to the headwall (and required an electrical outlet). The LCD monitor displays colour information about patient surface pressure on the bed and provides risk information determined by the length of time pressure had persisted in any location.

## **Objectives**

The primary objective of this study is to:

1. establish the effectiveness of a pressure-sensing mattress system (ForeSite PT™ system) in its ability to reduce interface pressure as reflected in a composite of pressure measurements.

Ethics ID number: REB13-0794

Study Title: Effectiveness of a pressure-sensing mattress system for reducing the risk of pressure ulcer formation by lowering interface pressure in vulnerable patient populations: Parallel-two-group randomized trial

PI: [name]

Version number/date: V2 01/04/2014

The secondary objectives are to:

1. assess whether the ForeSite PT™ system reduces the incidence of pressure-related compromised skin and soft tissues, with potential for progression to overt pressure ulceration;
2. determine the minimum interface pressure that is associated with higher risk for pressure ulcer development through the correlation of clinical outcomes and pressure outcomes;
3. assess healthcare provider and patient perceptions of the ForeSite PT™ system; and
4. establish the cost-effectiveness of the ForeSite PT™ system.

Specifically, the study will address the following research questions:

1. Is the ForeSite PT™ system effective at reducing interface pressure by assisting healthcare providers in determining the best method for patient turning/repositioning?
2. Does the use of the ForeSite PT™ system reduce the incidence of pressure-related compromised skin and soft tissues, with potential for progression to overt pressure ulceration?
3. Does interface pressure correlate with clinical outcomes?
4. Does the ForeSite PT™ system have more impact on the clinical outcomes of patients who have been identified as having a higher risk of pressure ulceration as per the Braden scale?
5. What are the perceptions (both positive and negative) of healthcare providers to the ForeSite PT™ system with regards to functionality, ease of use, and interpretation of pressure data on the computer monitor?
6. What are the perceptions (both positive and negative) of patients (and if appropriate, family members) to the ForeSite PT™ system (including sensor pad and monitor display of their pressure points)?

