## 190 **Outcomes**

### 191 **Primary Outcome**

- 192 1. A composite of interface pressure measurements that reflect the distribution of interface pressure  
193 at predetermined time intervals. These measures include:
- 194 a. proportion of participants that have pressure readings greater than 40 mmHg;
  - 195 b. average interface pressure (excluding sensels with 0mmHg reading); and
  - 196 c. the absolute number of sensels with pressure readings greater than 40 mmHg.

197 The measurement of this outcome will be facilitated by the ForeSite PT™ system's sensor overlay that  
198 continuously collects pressure readings. The array of the sensor overlay is a capacitive sensor with a  
199 0.625" spatial resolution. There are 52 rows x 118 columns for 6,136 sensing points. The ForeSite PT™  
200 system's software continuously samples interface pressure at a rate of 1 Hz, which can then be  
201 extracted for analysis. The data file is in a proprietary binary format, and can be exported to TXT or CSV  
202 formats for import into a spreadsheet program for analysis. This will be achieved by the sampling of  
203 pressure readings at specified time intervals before and after turning/repositioning when the ForeSite  
204 PT™ system's LCD monitor is turned on, and when it is turned off.

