## 291 **Analysis and Statistical Methods**

292 Subjects will be stratified by their pressure ulcer risk, as determined by their Braden Score.

293 Data analysis will involve use of Chi-square and/or Fisher exact tests for between-group (i.e.,  
294 intervention and control groups) comparisons of the primary outcome and the secondary outcomes, and  
295 the Wilcoxon rank sum test for between-group comparison of strategic shifting. Chi square and t-tests  
296 will be used to compare baseline characteristics between groups, and logistic regression will be used for  
297 adjusted analyses if there are notable between-group differences for important baseline characteristics.  
298 Correlation between pressure distribution (the study's primary endpoint) with the hard clinical outcome  
299 (pressure ulceration and pressure-related skin appearance changes) will also be explored.

300 Univariate statistics will be used to summarize changes in pressure distribution as per the interface  
301 pressure feedback provided by the ForeSite PT™ system.

302 Univariate statistics will be used to summarize close-ended survey data, while open-ended survey data  
303 will be thematically analyzed.

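### Secondary objective 2 promises a minimum harmful interface pressure, but the stated method (a correlation) and the declared pressure measures cannot return one

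*Protocol*

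**What the plan says.** Four places in the protocol bear on this point.

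- **Objectives, secondary objective 2:** "determine the minimum interface pressure that is associated with higher risk for pressure ulcer development through the correlation of clinical outcomes and pressure outcomes". This names both a target (a minimum pressure) and a means (correlation).
- **Objectives, research question 3:** "Does interface pressure correlate with clinical outcomes". This asks only whether an association exists.
- **Primary Outcome:** three measures are listed. (a) is the "proportion of participants that have pressure readings greater than 40 mmHg". (b) is the mean interface pressure with zero-reading sensels left out. (c) is "the absolute number of sensels with pressure readings greater than 40 mmHg".
- **Analysis and Statistical Methods:** "Correlation between pressure distribution (the study's primary endpoint) with the hard clinical outcome" is to be explored. No other analysis links pressure to skin findings.

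The raw data are much richer than the three measures. Of the sensor array the protocol says "There are 52 rows x 118 columns for 6,136 sensing points". Readings are taken at 1 Hz and can be exported. Under Secondary Outcomes, the Research Nurse circles affected skin areas on a form, so lesion site is recorded.

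**The concern.** The objective asks at what pressure risk begins to rise. The method answers how strongly pressure and outcome move together. These are different questions, and the second does not contain the answer to the first.

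The choice of pressure variable makes this worse. The analysis section equates pressure distribution with the primary endpoint, and two of that endpoint's three measures have 40 mmHg built in. If patients above 40 mmHg turn out to have more skin changes, 40 mmHg could be read as the harmful level simply because no other level was examined. The Discussion in the abstract expects the results to inform clinical practice guidelines, so a threshold reported on that basis could be taken up elsewhere.

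**Working it through.** **The plan's own figure.** The protocol gives no number for objective 2. Its one computed figure, 294 per arm, reproduces from 30% versus 20%, two-sided alpha 0.05 and 80% power with pooled variance:

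[1.96·√(2·0.25·0.75) + 0.8416·√(0.3·0.7 + 0.2·0.8)]² / 0.10² = (1.2003 + 0.5119)² / 0.01 = 293.2, rounded up to 294.

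That figure concerns the primary outcome and has no bearing on this point.

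**What each declared measure can show**

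| Measure | Form per patient | What its relation to skin outcome can show |
|---|---|---|
| (a) any reading above 40 mmHg | yes/no | whether exceeding 40 goes with risk; no other level |
| (b) mean over non-zero sensels | continuous, no location | association with average pressure; a cut-off search is possible but is not a correlation, and yields a level of average pressure |
| (c) number of sensels above 40 mmHg | count, no location | whether more area above 40 goes with risk; no other level |

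Measure (a) is worded as a group proportion. To enter a correlation across patients it has to be read as each patient's yes/no indicator.

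**Illustration of the logic, with assumed inputs.** None of the following comes from the protocol. Give each patient one pressure X, uniform on 20 to 80 mmHg (SD 60/√12 = 17.32), and a lesion risk of 10% below and 30% above a true threshold T.

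*Measure cut at 40 mmHg.* Lesion risk below versus above 40 is:

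- T = 30: below, ½·0.10 + ½·0.30 = 0.20; above, 0.30.
- T = 40: below, 0.10; above, 0.30.
- T = 65: below, 0.10; above, 0.10 + 0.20·(15/40) = 0.175.

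Risk is higher above 40 mmHg in all three cases, although the true threshold is 40 in only one. The table at 40 cannot tell them apart without knowing the two risk levels.

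*Continuous pressure with a correlation coefficient.* Here cov = 0.2·(T−20)(80−T)/120, and the lesion proportion is p = 0.1 + 0.2·(80−T)/60. Then r = cov / (17.32·√(p(1−p))).

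- T = 30: 0.833 / (17.32·0.442) = 0.11
- T = 40: 1.333 / (17.32·0.423) = 0.182
- T = 55: 1.458 / (17.32·0.387) = 0.218
- T = 65: 1.125 / (17.32·0.357) = 0.182
- T = 75: 0.458 / (17.32·0.321) = 0.08

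The coefficient rises and then falls with T, so thresholds of 40 and 65 mmHg give the same value. This holds before any sampling error (SE about 1/√600 = 0.04).

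**A second assumed model.** Loaded-sensel pressures were simulated as lognormal with mean about 25 mmHg. Risk was 10% below and 35% above a threshold for the patient's local peak, with 20,000 patients per threshold. The correlation of outcome with average pressure was 0.08 at T = 50, 0.15 at T = 60, 0.19 at T = 65 and 0.15 at T = 90. Again two quite different thresholds (60 and 90) give nearly the same coefficient. About 99% of simulated patients had at least one reading above 40 mmHg, so measure (a) hardly varied; that share depends on the assumed pressures.

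**The case against.** **Correlation may be meant loosely, and the SAP may supply the model.** The protocol names no coefficient, and the word can mean relating two sets of outcomes. Splines, cut-off grids and covariates are usually SAP detail. This stands as far as the particular model goes: its absence is not the finding. But the objective itself fixes the means, and the analysis section ties it to the primary endpoint. A threshold is promised in one place and only an association is planned in the others, whatever the SAP holds.

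**Measure (b) is continuous and the raw readings are stored.** Correct. A reader might infer that the trial's data can never yield a threshold; the documents do not support that. The limitation lies in the declared measures and method. Nor is (b) an average over the whole mattress, because zero-reading sensels are excluded.

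**The illustrations rest on invented inputs.** Correct. In the first model r changes little for T from 40 to 65 but drops outside that range. In the second, T = 50 and T = 65 differ by 0.11, almost three standard errors at n = 600. The figures show that the coefficient does not map to one threshold. They do not measure the size of the problem in this trial.

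**Reverse causation.** A reader might also infer that the association is pulled toward zero because staff move patients once redness is seen. No section says that the record of the whole stay enters this analysis. Trial design speaks of measurement at baseline and on the last day, and Primary Outcome of sampling around repositioning. The claim is not supported and forms no part of the point.

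**Conclusion.** The point holds in this form: secondary objective 2 cannot be met by the method and measures that the protocol states for it. This follows from the wording and from what a correlation is, not from the assumed numbers above.

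Its reach is limited. It affects one secondary objective whose analysis the protocol calls exploratory. Research question 3, which asks only about association, can be addressed as planned. That 40 mmHg will be reported as the harmful level is a risk that the design of the measures invites, not a certainty. The change should be made, but nothing else in the trial depends on it.

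**What to change.** Choose one of two changes.

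1. **Restate the objective.** Word secondary objective 2 as describing the association between interface pressure and pressure-related skin changes, in line with research question 3 and the analysis section. This costs nothing beyond the wording.

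2. **Keep the threshold aim and change the method.** Replace the correlation with a dose-response analysis of the stored readings:
   - in patients free of the lesion at baseline, fit a logistic regression of a new lesion on continuous pressure exposure, for example with a spline;
   - repeat it for exposure above a range of cut-offs, not 40 mmHg alone;
   - adjust for arm and baseline Braden score;
   - report the curve with its confidence band, and claim a threshold only if the data support one.

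Matching exposure to lesion site would come closer to local pressure, but should be optional. The protocol does not say that exported files carry body-region labels, and linking bed-grid sensels to anatomy in patients who are turned may take real work.

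The second option costs some extra analysis of readings already collected. Its downside is precision. The event rates in the Sample size section are attached to the primary outcome, so the expected number of new lesions is not known. If there are few, the curve will be wide and the claim more modest.

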## **Methods**

### **Trial design**

A parallel two group randomized controlled clinical trial will be conducted to assess the use of ForeSite PT™ system on a pressure-related skin and tissue changes, with progression to pressure ulceration; interface pressure; and the perceptions of healthcare providers and patients to the ForeSite PT™ system. Eligible consenting inpatients will be randomly allocated to either have the ForeSite PT™ system and the LCD monitor turned on (intervention group), or have the ForeSite PT™ system and the LCD monitor turned off (control group) in a ratio of 1:1. Both groups will be included in the study up to a maximum of 7 days. Interface pressure and clinical outcomes will be measured at baseline (within 24 hours of admission) and on the last day of enrollment in the trial (within 24 hours prior to discharge, or on the seventh day (whichever comes first)). The perceptions of patients allocated to the intervention group, and the perceptions of healthcare providers each time a patient in their care is allocated to the intervention group, will be measured on the last day of enrollment in the trial or on the seventh day (whichever comes first).

Ethics ID number: REB13-0794

Study Title: Effectiveness of a pressure-sensing mattress system for reducing the risk of pressure ulcer formation by lowering interface pressure in vulnerable patient populations: Parallel-two-group randomized trial

PI: [name]

Version number/date: V2 01/04/2014

